### Recruitment and participants

Study participants will be recruited from the First Rehabilitation Hospital of Shanghai, China. Recruitment strategies will include posting research advertisements to the patients or their caregivers at multiples site in the hospital. Other recruitment methods include the use of word of mouth and social media. Interested patients or caregivers will be encouraged to contact research staff via telephone.

Patients will be included if they (1) are aged 18–65 years; (2) diagnosed with stroke by computed tomography or magnetic resonance imaging within 6 months following stroke onset [25]; (3) have a unilateral stroke for the first time; (4) have cognitive impairment (as determined via a Montreal Cognitive Assessment [MoCA] cut-off score of 26) [26, 27]; and (5) have severe upper limb functional deficits (Fugl-Meyer Assessment for Upper Extremity [FMA-UE]. 0–28) [23].

The exclusion criteria comprise the following: (1) severe visual, auditory, or speech impairments; (2) a history of epilepsy or serious heart, lung, liver, or kidney disease; (3) participation in robot-assisted training or other intervention programs in the past 3 months; and (4) inability to complete the entire intervention as required.

Participants will be considered withdrawal from the study if they (1) make a request to withdraw from the study; (2) show any serious adverse reactions to the robot-assisted therapy treatment; or (3) develop a serious disease that preclude them from continuing treatment.

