#### Other measures

These will include baseline demographic measures that assesse patient demographic characteristics (e.g., age, sex, stroke type [hemorrhagic/ischemic], educational level, affected side, time after stroke, handedness). In addition, history of disease will also be collected with a self-reported questionnaire.

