### Statistical methods

#### Sample size and power

The sample size in this study is based on the expected difference between the two intervention groups in the outcome measure of FMA-UE score. We based our intervention effect from the existing literature on the effects of robotic training involving patients with stroke. With a predicted medium size effect, our power calculation indicated that, with a sample size of 78 stroke patients, we will have statistical power of 80% (at a two-tailed significance level of 0.05) to detect a between-group mean difference at an effect size of 0.65 for FMA-UE [36]. Power calculations were performed using G_*_Power free software (Version 3.1.9.4). Assuming a 10% attrition rate, we plan to enroll a total of 86 patients.

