### Statistical methods for primary and secondary outcomes

With intention-to-treat, participants will be analyzed according to their assigned randomization group regardless of their participation status. Descriptive statistics will be performed to describe study population and patients’ demographical and clinical characteristics at baseline. Continuous variables and categorical variables will be presented as mean ± standard deviation or percentages, respectively. Baseline demographic descriptors will be compared across groups, using analysis of variance for continuous variables and the chi-square (or Fisher’s Exact) test for categorical variables.

For primary and secondary outcome analyses, we will use repeated measures analysis of variance (ANOVA) to compare pre- and post-intervention changes at 6-week follow-up in the repeated outcome measures (a within subject factor) between the two intervention groups (a between group factor). Analyses will be conducted with and without important adjustments for baseline covariates (e.g., age, gender, stroke type, affected side) using either ANOVA or analysis of covariance (ANCOVA) statistical models. Pre- and post-intervention change scores on the primary and secondary outcome variables and their 95 percent confidence intervals will be computed to determine the intervention effects. Two-sided *P* values of less than 0.05 will be considered to indicate statistical significance. No subgroup or supplemental analyses are planned. All statistical analyses will be performed using SPSS version 25 (IBM Corp., Armonk, NY, USA), with the significance level set at *p* ≤ 0.05.

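### The plan names repeated measures ANOVA but also commits to adjusted and unadjusted ANOVA or ANCOVA versions with an open covariate list, and no version is designated as deciding either primary outcome

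*Protocol article*

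**What the plan says.** The relevant text is in the Protocol article, Statistical methods for primary and secondary outcomes. It makes three statements about the same outcomes.

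- Repeated measures ANOVA, with time within subject and group between subjects, is named for primary and secondary outcomes.
- The analyses are described as "conducted with and without important adjustments for baseline covariates (e.g., age, gender, stroke type, affected side) using either ANOVA or analysis of covariance".
- Change scores with 95% confidence intervals will establish the intervention effect. The model they come from is not stated.

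No sentence says which version supplies the deciding P value, when ANOVA or ANCOVA applies, or whether the baseline score of the outcome enters as a covariate. The same section says no supplemental analyses are planned, so neither the adjusted nor the unadjusted version is marked as secondary to the other.

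The baseline data listed under Other measures include "educational level, affected side, time after stroke, handedness". Entry is open to patients diagnosed "within 6 months following stroke onset" (Recruitment and participants).

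**The concern.** Following the text literally gives at least two P values for each primary outcome, each judged at two-sided 0.05, with no rule for which one counts. The adjusted version is itself not unique, because its covariates are given only as examples. The headline could then depend on a choice made after the results are known, and the stated 5% would no longer describe the error rate.

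The second issue is efficiency. The one model that is clearly named works on change scores. Using the baseline score as a covariate instead is at least as precise in a randomised trial, and more precise unless the baseline happens to predict the 6-week value with a slope of one. The text does not commit to it.

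**Working it through.** **Inputs from the protocol (Sample size and power; Trial design).** Two-sided alpha 0.05 ("at a two-tailed significance level of 0.05"), 80% power, a standardised difference of 0.65 ("to detect a between-group mean difference at an effect size of 0.65 for FMA-UE"), 78 evaluable ("with a sample size of 78 stroke patients"), 86 enrolled ("Assuming a 10% attrition rate, we plan to enroll a total of 86 patients"), 1:1 allocation. Not stated, so assumed: pre-post correlation ρ from 0.3 to 0.85, and four covariates jointly explaining 10% or 30% of the residual variance.

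**Step 1: the plan's own figure.** Two-sample t-test with noncentral t, d = 0.65: 38 per arm gives 79.9% power and 39 per arm gives 80.9%, so N = 78. Attrition: 78 × 1.10 = 85.8, that is 86 (78 / 0.9 would give 87). The stated size reproduces and is not in dispute.

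**Step 2: what the named model is.** With two time points, the group-by-time test of a repeated measures ANOVA is the two-sample test on change scores. Adding covariates to it is equivalent to regressing the change score on group and those covariates.

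**Step 3: type I error if the version is left open.** Normal data, N = 78, no true effect, 8,000 runs for each of eight scenarios (ρ = 0.3, 0.5, 0.7, 0.85; covariates explaining 10% or 30%). Four models per data set: change score and baseline-score ANCOVA, each with and without the four covariates.

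| Rule | Type I error per outcome |
|---|---|
| One model fixed in advance | 4.5% to 5.5% |
| Better of unadjusted and adjusted repeated measures ANOVA | 6.2% to 7.5% |
| Best of all four models | 8.2% to 11.6% |

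The Monte Carlo standard error near 10% is √(0.10 × 0.90 / 8,000) = 0.3 percentage points, so the inflation is not simulation noise.

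**Step 4: how often the choice changes the answer.** Under no effect, unadjusted repeated measures ANOVA and fully adjusted ANCOVA disagree on significance in 4% to 7% of trials. At a true 0.65 SD effect with covariates explaining 10% (4,000 runs), they disagree in about 14% of trials at ρ = 0.5 and 3.5% at ρ = 0.7.

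**Step 5: power given up by the change score.** Take equal SDs at both visits, scaled to 1. The change score has SD √(2(1 − ρ)); the ANCOVA residual has SD √(1 − ρ²). Power at 39 per arm for a difference of 0.65 post-score SD is:

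| ρ | SD, change | SD, ANCOVA | Power, change | Power, ANCOVA |
|---|---|---|---|---|
| 0.3 | 1.183 | 0.954 | 66.8% | 84.4% |
| 0.5 | 1.000 | 0.866 | 80.9% | 90.5% |
| 0.7 | 0.775 | 0.714 | 95.5% | 97.8% |

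The direction does not depend on equal SDs. With baseline SD s₀ and 6-week SD s₁, the change-score variance exceeds the ANCOVA variance by s₀² + s₁² − 2ρs₀s₁ − s₁²(1 − ρ²) = (s₀ − ρs₁)², which is never negative. On the post-score scale, the change-score analysis keeps its planned 80% at N = 78 only if ρ is at least about 0.5, because √(2(1 − ρ)) ≤ 1 requires ρ ≥ 0.5.

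**The case against.** The strongest reply is that the section does name a main model. Repeated measures ANOVA comes first, and the next sentence can be read simply as ANOVA when unadjusted and ANCOVA when adjusted. That would be two versions rather than a free choice among many. The reading is fair, and it limits the inflation to the 6.2-7.5% row. It does not remove the gap, because naming a model first does not make it decisive over an adjusted version announced on equal terms. A reader might infer that no primary model is named at all; the text does not support that.

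A second reply concerns the covariates, and it stands. A reader might infer that time after stroke and educational level have been left out. The list is introduced as examples and both variables are collected, so neither is excluded. Nor does the article show that either predicts 6-week change. The defect is that the list is open.

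A third reply is that a final covariate list is commonly left to a statistical analysis plan that is not shown. That holds for the list alone. It does not hold for stating competing analyses of a primary outcome without ranking them.

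Two further inferences also go too far. The chance of a false positive on either primary outcome is well above 5%, but most of that comes from testing two outcomes: with one fixed model each and an assumed between-outcome correlation of 0.3, it is already about 9.5%. And chance baseline imbalance does not invalidate an unadjusted test, which already allows for it. The planned baseline comparisons are not said to select covariates.

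**Conclusion.** The point holds in limited form. Repeated measures ANOVA is named, but adjusted and unadjusted versions by ANOVA or ANCOVA are also promised, none is designated as deciding, the covariate list is open, and the outcome's baseline score is not named as a covariate.

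Selecting the better result would take type I error per outcome from 5% to 6.2-7.5% on the narrow reading and 8.2-11.6% on the widest. These are the consequences of selective quoting; nothing in the article says that selection is intended. The power cost of the change score is large at a low pre-post correlation (66.8% against 84.4% at 0.3) and small at a high one (95.5% against 97.8% at 0.7).

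The sizes rest on normal data, assumed correlations and covariate strengths, equal SDs at the two visits, and reading 0.65 as post-score SD units, which the article does not specify. If 0.65 is instead in change-score SD units, the change-score analysis has its 80.9%. With equal SDs, ANCOVA would then need a fraction (1 − ρ²) / (2(1 − ρ)) = (1 + ρ)/2 of the patients: 65%, 75% or 85% at ρ = 0.3, 0.5 or 0.7. The preference for ANCOVA is the same on either scale. The sample size itself is sound.

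**What to change.** Name one deciding analysis for each primary outcome. This would be ANCOVA of the 6-week value on randomised group and that outcome's own baseline value, plus a short closed list of covariates fixed before anyone sees outcomes by group. Draw the list from variables already collected. Time after stroke, and educational level for the cognitive outcomes, are worth considering alongside those already named as examples. Take the reported effect and its 95% confidence interval from this model. State that the repeated measures ANOVA and the unadjusted results are supportive and do not decide the trial.

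The cost is a few lines of wording and a few degrees of freedom. No new data and no more patients are needed, since 78 evaluable reproduces. The article gives the trial as still recruiting, so the change can be made and dated before analysis.

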**Methods:**

This will be a single-blinded, 2-arm, parallel design, randomized controlled trial which will include a sample size of 86 acute and subacute stroke patients to be recruited from a single clinical hospital in Shanghai, China. Upon qualifying the study eligibility, participants will be randomly assigned to receive either robot-assisted therapy or conventional therapy with both interventions being conducted over a 6-week period in a clinical rehabilitation setting. In addition to comprehensive rehabilitation, the robot-assisted therapy group will receive a 30-min Armguider robot-assisted therapy intervention 5 days a week. Primary efficacy outcomes will include Fugl-Meyer Assessment for Upper Extremity (FMA-UE) and Mini-Mental Status Examination (MMSE). Other secondary outcomes will include Trail Making Test (TMT), Auditory Verbal Learning Test (AVLT), Digit Symbol Substitution Test (DSST), and Rey–Osterrieth Complex Figure Test (ROCFT). All trial outcomes will be assessed at baseline and at 6-week follow-up. Intention-to-treat analyses will be performed to examine changes from baseline in the outcomes. Adverse events will be monitored throughout the trial period.

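### Two primary outcomes, FMA-UE and MMSE, are each tested at an unadjusted 0.05 with no rule linking them: if either can support an efficacy claim, the false positive chance is 7.0% to 9.75%; if both are needed, the 80% power does not describe trial success

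*Protocol article*

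**What the plan says.** The Methods part of the protocol article's abstract states: "Primary efficacy outcomes will include Fugl-Meyer Assessment for Upper Extremity (FMA-UE) and Mini-Mental Status Examination (MMSE"). The Primary outcomes section describes the same two measures, and the Objectives section gives upper limb function and cognition an objective each.

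The section Statistical methods for primary and secondary outcomes uses one model for all of them: "For primary and secondary outcome analyses, we will use repeated measures analysis of variance (ANOVA"). It sets one two-sided criterion, P "values of less than 0.05 will be considered to indicate statistical significance", and repeats it for all analyses, "with the significance level set at *p* ≤ 0.05". It gives no order of testing, no division of alpha and no adjustment.

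Sample size and power rests on one of the two primaries: "The sample size in this study is based on the expected difference between the two intervention groups in the outcome measure of FMA-UE score". For a standardised FMA-UE difference of 0.65 between the arms, the claim there is "we will have statistical power of 80% (at a two-tailed significance level of 0.05"). It gives no effect size and no power for MMSE.

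**The concern.** Planning and inference treat the primaries differently. The sample size is worked out as if FMA-UE were the only primary, with all of the 0.05 spent on it. The analysis section then gives MMSE the same standing and its own 0.05. A reader cannot tell what result would make the trial positive, and the two natural answers have different consequences:

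- **Either primary suffices.** There are two chances of a false positive claim, each at 5%, so the error over the pair exceeds 5%.
- **Both are required.** The error over the pair is controlled, but the stated power describes only one of the two results needed.

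This matters in practice because the Discussion presents cognition as the neglected area that the trial addresses. A significant MMSE beside a non-significant FMA-UE would be reported prominently, and the plan does not say what such a result would establish.

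**Working it through.** **Inputs from the protocol article.** Two primaries (abstract; Primary outcomes). Two-sided 0.05 for each test (Statistical methods for primary and secondary outcomes). Standardised effect 0.65 on FMA-UE, power 80%, 78 evaluable patients (Sample size and power). 1:1 allocation (Trial design), so 39 per arm. The article gives no correlation between the two test statistics, so a range is assumed.

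**Step 1. Reproduce the plan's figure.** A two-sample t-test with d = 0.65, two-sided alpha 0.05 and 80% power needs 38.1 per arm by the noncentral t distribution. This rounds up to 39 per arm, or 78. At 39 per arm the noncentrality is 0.65 × √(39/2) = 2.87, the critical value on 76 degrees of freedom is 1.99, and power is 80.9%. The stated 78 is reproduced, and it uses the full 0.05 for FMA-UE.

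**Step 2. Error if either primary suffices and neither is affected.** For independent tests: 1 − (1 − 0.05)² = 1 − 0.9025 = 0.0975.

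For correlated tests, with (Z1, Z2) bivariate normal with correlation r, the error is 1 − P(|Z1| < 1.96 and |Z2| < 1.96):

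| Assumed r | At least one false positive primary |
|---|---|
| 0 | 9.75% |
| 0.3 | 9.5% |
| 0.5 | 9.1% |
| 0.7 | 8.3% |
| 0.9 | 7.0% |

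These figures count false positives in both directions. Counting only false claims in favour of the robot arm gives 4.9% at r = 0, against 2.5% for a single test, so the near-doubling is the same.

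**Step 3. If both primaries are required.** A false claim then needs at least one truly null test to reject, so the error is at most 5%. The probability of success cannot exceed the power of the weaker test. For MMSE that power is unknown, because the article gives no MMSE effect. The 80% therefore applies to FMA-UE and not to trial success.

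**Step 4. What the repairs do.**

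- *Fixed sequence, FMA-UE then MMSE, each at 0.05.* If FMA-UE is truly null, any claim requires a false rejection on it, which has probability 5%. If FMA-UE is truly affected, the only possible false claim is MMSE at 5%. Familywise error is at most 5%, and FMA-UE keeps its 80.9% power.
- *Holm across the two.* The smaller P value is tested at 0.025 and, if that rejects, the other at 0.05. FMA-UE is always tested at 0.025 or more. At 0.025 the critical value is 2.29 and power with 39 per arm and d = 0.65 is 71.9%, so FMA-UE power is at least 71.9%. Guaranteeing 80% at 0.025 would take 47 per arm, or 94 evaluable instead of 78.

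**The case against.** The strongest reply is that the Objectives section poses two separate questions, each with its own primary outcome. If each is answered on its own terms, the error per question is 5%. The article states 0.05 as a threshold for a test and nowhere promises 5% for the trial as a whole. Whether two distinct questions in one two-arm trial need joint control is partly a matter of judgement. A testing order may also stand in an analysis plan that is not shown.

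Part of this stands. A reader might infer that the trial has a false positive rate of nearly 10% where 5% was promised. The document does not support that. The near-10% figure requires that either outcome suffices, that neither is affected and that the tests are weakly correlated. The Background reports that motor performance is associated with global cognition, so independence is not the natural case.

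The reply does not dispose of the point. Study innovation and Conclusions frame a single conclusion about the therapy, covering physical and cognitive function together, which invites an either-outcome reading. Nor does the point depend on a missing detail, since the article itself fixes 0.05 for every outcome and spends the full 0.05 on FMA-UE. An unseen plan that split alpha would contradict both statements. One that required both outcomes would leave the 80% short of trial success.

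Two further inferences are tempting and should be resisted. One is to put a familywise error on the secondary scores. That would need independence among scores from the same tests (five AVLT scores, two TMT parts), which is implausible, and nothing lets a secondary score decide the trial. The other is to quote a joint power for both primaries. That would need an MMSE effect size, which the article does not give.

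**Conclusion.** The point holds in conditional form. The plan leaves the relation between its two primaries undefined, and one of its stated properties weakens under either reading. If either primary can support an efficacy claim, the chance of at least one false positive primary is 9.75% with independent tests and 7.0% at an assumed correlation of 0.9. Every value in that range is above 5%. If both are required, the error is at most 5% but the 80% power is not the power for success. The error figures assume no effect on either outcome and approximately normal test statistics. The power figures assume 39 evaluable patients per arm and the plan's effect of 0.65. Trial status says that recruitment is under way, so the rule should be settled before outcomes are compared.

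**What to change.** In Statistical methods for primary and secondary outcomes, add wording along these lines: FMA-UE will be tested first at two-sided 0.05. MMSE will be tested at two-sided 0.05 as a confirmatory outcome only if FMA-UE is significant; otherwise it will be reported as an estimate with its 95% confidence interval. TMT, AVLT, DSST and ROCFT results are supportive. This agrees with the sample size section as it stands.

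The change costs a few sentences and no patients. The real price is that a cognitive benefit could not be claimed alone if FMA-UE failed, which matters in a trial whose stated novelty is cognition. If the investigators want either objective to be claimable alone, they should name Holm across the two primaries and restate FMA-UE power in Sample size and power as at least 71.9% at 78 evaluable patients. If they intend both to be required, they should say so and state the MMSE effect on which power for trial success depends. The choice is theirs, but one rule should be written down.

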#### Adverse event reporting and harms

Current literature on the use of robotic-assisted rehabilitation therapies has not reported any serious or major harms resulting from their administration to patients with stroke. However, we will take every precaution to monitor and record any adverse events (including minor, moderate, or serious events), either intervention or non-intervention related, during the entire course of our study and report them, in a timely manner, to the ethics committee and relevant regulatory agencies.

## Discussion

Current consensus from stroke survivors, caregivers, and health professionals has identified that upper limb and cognitive dysfunction in patients with stroke are among the top 10 priorities that need to be addressed in clinical research and practice [37]. Robot-assisted therapy is an emerging therapeutic approach for enhancing the recovery process and providing safe, repetitive, high-intensity, and task-specific rehabilitation interventions [38]. Previous studies have primarily focused on examining the effects of robot-assisted therapy on motor recovery function with relative little attention paid to the importance of cognitive function for stroke patients [18–23]. Cognitive function has been implicated as playing a crucial role in post-stroke mobility recovery and, therefore, needs to be taken into account as part of integral clinical treatment [10–12]. This trial is designed to specifically address this major gap in research and, more importantly, responds to current treatment needs that have been identified in clinical practice [37]. To understand potential cognitive benefits of robot-assisted therapy, we will use multiple assessment tools to comprehensively evaluate the cognitive domains ranging from global cognitive function to domain-specific cognition, including the areas of executive abilities, working and visual memory, attention, information processing speed, visuospatial abilities.

